**Treatment**

Blue light

The subjects will be continuously exposed of 460-480 nanometers monochromatic light for 4 hours during nighttime driving.

The Apollo goLite M2 with Long Lasting Eye Safe LEDs technology will be fixed in the car. This product, CE Safety Tested, is distributed by Respironics-Philips and used in many countries. This device produces no UV or near-UV light, and passes ocular safety testing as well as all government and industrial ocular standards

Coffee

Each participant will drink 125 ml of coffee (about half a cup of coffee, containing 200 mg of caffeine) or 125 ml of placebo (containing 15 mg of caffeine) 30 minutes before the nighttime driving session and after 2 hours of driving.

Coffee and placebo will be prepared from single packs of the relevant instant coffee (normal or decaffeinated) provided by Nestlé. Coffee contains 4.25% caf­feine and placebo (decaffeinated coffee) contains less than 0.3% caffeine. Placebo and coffee will not distinguishable by taste or appearance.

**Criteria of assessment**

Primary efficacy criterion

- Number of inappropriate line crossings (ILC) identified from the video recordings.

Secondary efficacy criteria

- Standard deviation of the position of the car
- Self-rated sleepiness during driving
- Self-rated fatigue during driving
- Sleep latency during the subsequent sleep
- Sleep efficiency during the subsequent sleep
- Time course of EEG slow wave activity during the subsequent sleep

Secondary criteria

- Chronotype
- Caffeine sensitivity
- Habitual sleep patterns
- PER3 polymorphism
- COMT polymorphism
- ADORA2A polymorphism
- Reaction time and percentage of errors at cognitive tests
- Saliva cortisol concentration before and after the driving session and after the sleep recovery.
- Saliva amylase concentration before and after the driving session and after the sleep recovery.

**Clinical assessment methods**

EFFICACY

Driving session

Driving conditions will be a straight highway on weekdays with usually light traffic conditions, in fair weather. All drivers will be exposed to the same or very similar conditions. During a training session, participants will be instructed to maintain a constant speed (130 kph [80 mph]), to drive in the center of the lane, and not to cross the painted lines separating the lanes except to pass a slower vehicle.

During the whole experiment, a professional driving instruc­tor will monitor the driving speed. He will be ready to take control of the car (equipped with dual controls) if needed. If a participant could no longer drive during a session, he will drive back to the rest area. The car used for the experiment will be equipped with a video system that calculates the driving ability.

The main outcome measure will be the number of inappropriate line crossings (ILC) identified from the video recordings. This measure was selected because epidemiologic findings have shown that 65% of sleep-related accidents occur after an ILC (Sagberg 1999). Several studies have also shown that impaired daytime alertness induces lateral devia­tions during driving (O'Hanlon and Volkerts 1986; Ramaekers and O'Hanlon 1994; O'Hanlon, Vermeeren et al. 1995) and that sleep-related accidents frequently occur with a single car driving off the road and hitting an obstacle with no reaction from the driver (Pack, Pack et al. 1995; Sagberg 1999). We have also demonstrated that the number of ILCs is affected by sleep deprivation (Philip, Sagaspe et al. 2005; Philip, Sagaspe et al. 2005) and improved by classic countermeasures to sleep loss (Philip, Taillard et al. 2006).

An ILC is recorded when the car cross a lateral highway lane marker, as evidenced by video-recording analysis. Exceptions are overtaking manoeuvres or some other necessary driving action, as recorded by the driving instructor. Driving-instructor and video-recording timelines were synchronized at the beginning of each ses­sion. Deviations related to traffic interference will be excluded so as to concentrate on line crossings related to driver status.

The second outcome measure will be the standard deviation of lateral position. It is reasonable to assume that SDLP represents overall highway driving ability since it encompasses several levels of information processing which are combined to an integrated driving model (Ranney 1994). For example, basic vehicle control, such as road tracking, is required involving automatic or effortless performances. Further, negotiation of common driving situations, such as curves, intersections, and gap acceptance, requires controlled processing, which is more effortful. Since SDLP increment ultimately results in lane crossing into the adjacent traffic lane, SDLP can be regarded as an index of driving safety. Furthermore, this test is performed during normal traffic; hence, the on-the-road driving test is a close representation of normal driving.

Subjective sleepiness

Participants will be asked to rate their sleepiness on the Karolinska Sleepiness Scale (a 9-point scale from 1 = “extremely alert” to 9 = “very sleepy, great effort to keep alert, fighting sleep”).

Subjective fatigue

Participants will be asked to rate their instantaneous fatigue (“de­scribe how fatigued you are now” on a 100-mm visual analogue scale from 0 “not at all tired” to 100 “very tired”).

Polysomnography

Three electroencephalograms (F3/A2, C3/A2, O1/A2), 1 electromyogram, 2 electrooculograms, and 1 electrocardiogram will be recorded dur­ing the night after driving.

Signals will be digitized at a sampling rate of 256 Hz and filtered with a digital filter at a cutoff frequency of 35 Hz.

Data will be manually analyzed by an experienced sleep technician in 30-second epochs according to Rechtschaffen and Kales’ recommendations (Rechtschaffen and Kales 1968). Non-rapid eye movement (NREM) sleep (stages 2, 3, and 4) during sleep will be retained for spectral analysis. Electroencephalographic signals of C3/A2 derivation will be subjected to analysis by fast Fourier transforma­tion. Power spectra will compute for consecutive 2-second epochs, providing a frequency resolution of 0.5 Hz. The delta frequency band (0.5-4.5 Hz) will be exploited.

SUBJECTS TYPING

Genomic (PER3, COMT, ADA, ADORA2A) DNA

Genomic DNA will be extracted from 2*5ml blood sample (tube with EDTA solution).

Saliva cortisol and amylase

Saliva will be directly collected from mouth to tube. Samples will be stored at -18°c before analysis. Saliva cortisol and amylase concentrations will be determined by RIA.

Caffeine sensitivity assessment

Subject reporting nocturnal sleep disturbances after caffeine intake in the afternoon will be considered as caffeine sensitive and subject reporting no problems sleeping after caffeine in the afternoon were considered as caffeine insensible.

Cognitive tests : Evaluation of attentional components

*- Tonic and phasic Alertness*: The examination includes a simple and a cued reaction time task with a visual test stimulus and an acoustic cue. The difference between simple and cued reaction time is a measure of phasic alertness. (Computerized test)

- *Vigilance and sustained attention*: There are four tasks with different stimuli (3 unimodal tasks: 1 acoustic, 2 visual; one bimodal task: visuo-acoustic) that assess sustained attention or vigilance. Each task can be run with high (sustained attention) or low event rate (vigilance) of critical stimuli. (Computerized test).

*- Divided attention*. A dual task is used. The visual task consists of crosses that appear in a random configuration in a 4 x 4 matrix. The subject has to detect whether the crosses form the corners of a square. The acoustical task includes a regular sequence of high and low beeps. The subject has to detect an irregularity in the sequence. (Computerized test).

- Selective attention (Zazzo’s cancellation task, short 8-line version). This test measures the ability to cross out as fast and as exactly as possible target signs among distracters on a sheet of white paper containing 8 lines of signs. In our study, we considered the time spent to complete all 4 lines and the omission errors and false alarms. (Pen-paper test)

Cognitive test : Evaluation of executive functions

Inhibition

- Go/No-Go: this test requires a subject to emit a simple motor response (Go) to one cue while inhibiting the response in the presence of another cue (No Go). There are twice more Go signals than No-Go signals. Reaction time and percentage of error will be measured.

- Incompatibility: during incompatibility task , the tendency of interferences will be tested by a Stimulus-Responses incompatibility. Subjects were instructed to squeeze as fast as possible in response to a left- or right-pointing arrow presented on a computer screen. The arrow determined whether the response was to be compatible (e.g., right arrow with right hand squeeze) or incompatible (right arrow with left hand squeeze). Reaction time and percentage of error will be measured in the two conditions.

Cognitive speed

- The Trail Making Test (TMT) R. Reitan, Trail Making Test: manual for administration and scoring, Reitan Neuropsychology Laboratory, Tuscon, AZ (1992) is used to assess cognitive speed, visual motor tracking, divided attention, and mental flexibility. It consists of two parts. In Part A, the participant has to connect numbers from 1 to 25 in the correct order as fast as possible (cognitive speed and visual motor tracking). (Pen and paper test). The score was total duration in seconds and the number of correct moves.

- The Digit Symbol subset of the WAIS-R is used to measure coding ability. This test is a performance measure which requires the subject to code nine simple symbols matched with nine numerals. The subject is given 90 seconds to code all items on the test. (Pen and paper test)

Flexibility

- TMT-B : numbers from 1 to 13 and letters from A to M must be connected in alternating fashion, beginning at 1-A and ending at M-13. Total score is given by time spent to complete each part (Pen and paper test)

- TEA Flexibility : Two stimuli (letter and digit) are displayed at a time. Subjects will be instructed to push on right or left key in according to the target. (Computerized test)

Working Memory

Updating memory task. Subjects must recall digit number list.

SELECTION

Actigraphy

Actimeters will be used to quantify our volunteers’ sleep duration and quality. This device monitors body movements and allows calculation of mean nocturnal sleep episodes and of nocturnal awakenings. Time in bed will be also computed as the time difference between going to bed in the evening and getting up in the morning. Sleep efficiency will be calculated as the ratio of time asleep to the time in bed, in percentage. To rule out any sleep-wake schedule disorders each subject will be monitored for 7 days before being included in the study. Subjects will be included if they have a mean sleep efficiency of at least 85% during the 7 days of recordings.

Polygraphy

A nocturnal polygraphy (nasal flow, oxygen saturation, two respiratory effort belts, snore, position, leg movement) will be performed to eliminate subjects suffering from sleep disorders. Subjects presenting an AHI > 5 for the 20-25 years old and > 10 for the 40-50 years old or a PLM index >15 will be excluded of study.

Habitual sleep patterns

The evaluation of usual sleep schedules, sleep quality, sleep needs and sleep hygiene will be assessed by the Basic Nordic sleep questionnaire. This 22-items questionnaire evaluate the quality of sleep over the previous 3 months as measured by a frequency scale ranging from 0 (never or less than once a month) to 5 (almost everyday or everyday) (Partinen and Gislason 1995).

Chronotype assessment

The chronotype will be assessed by Horne and Ostberg questionnaire (Horne and Ostberg 1976). This questionnaire contains 19 items about individual rising and bedtimes preferred time of physical and mental performances and alertness after rising and before going to bed. It mainly use 4-choices items.

Sleepiness

Chronic daytime sleepiness will be assessed by the Epworth Sleepiness Scale wich rates the tendency to fall asleep in 8 different situations in daily life.

Self-reports symptom inventory SCL-90R

The evidence of psychopathology will be assessed by the Symptom Checklist 90 (SCL-90). This questionnaire is a psychiatric self-report inventory. The 90 items in the questionnaire are scored on a five-point Likert scale, indicating the rate of occurrence of the symptom during the time reference. It is intended to measure symptom intensity on nine different subscales. It has been shown to have a good reliability as its internal consistency is high.

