**Study design**

Experimental design

This is an interventional study: Double-blind (except for blue-light), Randomized, Crossover, Comparative versus referent countermeasure of sleepiness: coffee (2*200 mg of caffeine) and placebo.

The study is divided into the following periods:

1. **selection period** without treatment between selection and inclusion visits to check the absence of exclusion criteria with questionnaires, polygraphic recording (respiratory sleep disorders and periodic leg movements) and actimetry (sleep efficiency, total sleep time)
2. **acute treatment period**, each volunteer will be randomly allocated to successively and randomly receive either continuous blue light exposure or 2*200 mg of caffeine or placebo of caffeine during night driving with at least 1 week between treatment.

Experimental protocol

SELECTION

Participant will complete the French version of the Basic Nordic Sleep Questionnaire (BNSQ), the self-report symptoms inventory SCL-90R, the chronotype questionnaire of Horne and Ostberg, the Epworth sleepiness scale. They will to have 7 consecutive days monitoring using actimeters and 1 night using polygraph.

INCLUSION

Participants will be screened for eligibility criteria. They will sign informed consent, perform cognitive tests, complete the caffeine sensitivity questionnaire. Blood samples will be collected.

DRIVING SESSION

Each subject, will come at the laboratory at 9:30 PM, and will kept awake until the time of the experimental session.

For each driving session (Blue light, caffeine and placebo of caffeine), all participants will drive 400 km (250 miles) on the same 2-lane highway for 4 hours. After 2 hours of driving (200 km, 125 miles) subjects will take a 15-minutes break. The night-time driving session will start at 1:00 AM and Stop at 5:15 AM. At the beginning, middle and end of the driving, participants will be asked to rate their instantaneous fatigue and sleepiness. After driving, sleep recuperation will be recorded in laboratory during a minimum of 6h. Saliva will be collected before and after the driving session and after sleep recuperation.

The subjects were instructed to maintain a regular sleep-wake schedule and were monitored by actimetry during the 3 days preceding each experimental session and during the 3 days after each experimental session.

**
[figure not shown]
**

C: Coffee

P: Placebo

BL: Blue Light

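### Exclusions from the primary line-crossing count rest partly on the open-ended log of an in-car instructor who can hardly avoid seeing the blue light, and no masked classification is stated

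*Protocol*

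**What the plan says.** The primary criterion (Protocol, Criteria of assessment) is: "Number of inappropriate line crossings (ILC) identified from the video recordings". Detection is by video (Protocol, Clinical assessment methods, Driving session): "An ILC is recorded when the car cross a lateral highway lane marker, as evidenced by video-recording analysis".

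The same section then sets two routes by which a detected crossing leaves the count:

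- The first depends on the instructor: "Exceptions are overtaking manoeuvres or some other necessary driving action, as recorded by the driving instructor".
- The second names nobody: "Deviations related to traffic interference will be excluded so as to concentrate on line crossings related to driver status".

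Between these two statements the section says that the instructor's and the video timelines are synchronised at the start of each session.

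On masking, Study design describes the trial as "Double-blind (except for blue-light), Randomized, Crossover". Under Treatment, coffee and placebo are said to be indistinguishable by taste and look. For the lamp, the same section states "The Apollo goLite M2 with Long Lasting Eye Safe LEDs technology will be fixed in the car", with subjects "continuously exposed of 460-480 nanometers monochromatic light for 4 hours during nighttime driving". Of the instructor, Clinical assessment methods says: "He will be ready to take control of the car (equipped with dual controls) if needed".

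**The concern.** Detecting a crossing on video is close to objective. Deciding that a crossing was justified is not, once the rule goes beyond overtaking. The residual category has no definition or list, and what falls into it depends on what the instructor chooses to log. He sits in the car with the lamp, so he can hardly fail to know which sessions are blue-light sessions. The other two sessions he cannot tell apart, provided he is also kept unaware of the drink.

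The primary objective compares blue light with coffee and with placebo, and both comparisons cross this boundary. A systematic difference in what is excused goes straight into the count. Randomisation, the crossover and the sample size do not remove it, and the negative binomial model analyses whatever count it receives. Coffee against placebo is not affected in this way.

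**Working it through.** The point concerns how the outcome is ascertained. It rests on no figure in the protocol, so there is none to reproduce. The check has two parts.

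**1. The text, set side by side**

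| Question | What the protocol gives | Where |
|---|---|---|
| Who detects a crossing? | Video analysis | Criteria of assessment; Clinical assessment methods |
| Who records overtaking and other necessary actions? | The driving instructor | Clinical assessment methods |
| Is the residual exception defined? | No | Clinical assessment methods |
| Who judges traffic interference, and by what rule? | Not stated | Clinical assessment methods |
| Can excused events be traced on the footage? | Yes, timelines are synchronised | Clinical assessment methods |
| Is blue light masked? | No, by declaration | Study design |
| Where is the lamp, and for how long is it on? | In the car, throughout the drive | Treatment |
| Where is the instructor? | In the same car, at dual controls | Clinical assessment methods |
| Is a masked classification of crossings stated? | No | – |

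That the instructor sees the lamp is an inference, but a firm one.

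**2. What unequal exclusion does to the IRR (illustration only)**

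Let e_BL and e_ref be the shares of true inappropriate crossings wrongly excluded under blue light and under the comparator. The expected count in each arm is multiplied by (1 − e), so

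apparent IRR = true IRR × (1 − e_BL) / (1 − e_ref).

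The protocol gives no values for either share. All values below are assumptions, with true IRR = 1:

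| e_BL | e_ref | Calculation | Apparent IRR |
|---|---|---|---|
| 5% | 0% | 0.95 / 1.00 | 0.95 |
| 10% | 0% | 0.90 / 1.00 | 0.90 |
| 20% | 0% | 0.80 / 1.00 | 0.80 |
| 15% | 10% | 0.85 / 0.90 | 0.944 |
| 20% | 10% | 0.80 / 0.90 | 0.889 |
| 30% | 10% | 0.70 / 0.90 | 0.778 |
| 0% | 10% | 1.00 / 0.90 | 1.111 |
| 10% | 20% | 0.90 / 0.80 | 1.125 |

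The last two rows show stricter scoring under blue light, which pushes the ratio above 1.

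The formula also gives a limit. If at most a share e of true crossings can be wrongly excluded in any arm, the distortion factor lies between (1 − e) and 1/(1 − e). For e = 5% that is 0.95 to 1.05, and for e = 20% it is 0.80 to 1.25. The bias is therefore small if the discretionary category is rarely used. If the two shares are equal, it is nil.

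The formula covers wrongly excluded crossings only. Justified crossings wrongly kept in the count would raise an arm's count and are not modelled here.

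**The case against.** - **The instructor logs events; he is not shown to adjudicate them.** This stands. The text describes a record made during the drive and matched to the footage. A reader might infer that he reviews detected crossings and waives some, but the protocol does not say so. The synchronised timelines also let an excused event be traced. Still, whether an action enters the log as necessary remains his judgement, and no masked check of it is stated.
- **Traffic interference is not assigned to the instructor.** This stands too. A reader might attribute that exclusion to him, but the sentence names nobody. The fault there is a missing criterion and a missing owner.
- **The scope is narrow.** The drive is on a straight highway at night, on weekdays, with usually light traffic and fair weather, and overtaking is a concrete event that can usually be checked on film. This is fair and may keep the discretionary share low. It limits the likely size of the bias but does not remove the route.
- **The open status of blue light is declared, and the instructor is there for safety.** Correct. His knowledge of the session cannot be avoided. What can be changed is the list of exceptions and who applies it.
- **The analysis plan or a scoring manual, not shown here, may cover this.** Masking of video files might be described there, and the absence of a sensitivity analysis from the protocol is not itself a fault. The exception rule, however, is written into the protocol and belongs to the definition of the primary outcome.

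**Conclusion.** The concern holds in a limited form. Detection is by video, but part of what is removed from the primary count rests on an undefined category, logged by someone who can hardly avoid knowing the blue-light sessions. A second exclusion has no rule and no owner. Exclusions can therefore differ between blue-light and masked sessions and bias both blue-light IRRs.

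The size is unknown. Under assumed shares of 10% against 0%, or 20% against 10%, a true IRR of 1 would read 0.90 or 0.89. With stricter scoring under blue light it would read above 1.

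A reader might conclude that blue light will be scored more leniently, especially since Expected results anticipates a benefit over placebo and an effect equal to coffee. The protocol does not support that step. It gives no exclusion shares and nothing to indicate a direction. The finding is an avoidable route for bias, not demonstrated bias.

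**What to change.** In Clinical assessment methods (Driving session):

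- Replace the open-ended exception and the traffic-interference sentence with one closed list of exceptions that can be verified on the footage: overtaking, road works, and a visible obstacle or visible traffic.
- State that the list is applied during the video analysis, with session label and treatment masked as far as the footage allows.
- Use the synchronised instructor log only to locate events on the recording. His safety role is unchanged.
- Report a sensitivity count of ILC that excludes overtaking crossings only.

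The cost is a rewritten paragraph and relabelled video files. The downside is that some justified manoeuvres not visible on video stay in the count. The protocol does not say what the camera shows or whether a person or a system reads the recordings, so full masking and the staff time it needs cannot be taken for granted. If masked footage is not feasible, the closed list and the sensitivity count should still be adopted.

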**Study objectives**

Primary objective

To compare the effects of continuous blue light exposure during driving with those of coffee (2*200 mg of caffeine) and coffee placebo on 4h night-time driving performance in young (20-25 years) and middle-aged (40-50 years) healthy volunteers

Secondary objectives

To determine the effect of age in the effectiveness of countermeasures (blue light and coffee)

To determine individual differences (cognitive, genetic and hormonal) in the impairment of neurobehavioral functions from sleep loss and in the effectiveness of countermeasures (blue light and coffee)

To determine the effects of blue light on quality and quantity of sleep after night-time driving in young and middle-aged healthy volunteers

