**Expected results**

- Improvement of nocturnal driving ability with countermeasures to sleepiness (coffee and continue blue light exposure) versus placebo in young and middle-aged healthy volunteers.

- Same beneficial effect of continue blue light exposure versus coffee on nocturnal driving ability in young and middle-aged healthy volunteers.

- Characterization of biological (genetic, cognitive or hormonal) markers explaining inter-individual variability in nocturnal driving impairment and effectiveness of countermeasures to sleepiness.

- Modifications on quality and quantity of sleep after the blue light exposure during nighttime driving in young and middle-aged healthy volunteers.

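### The blinding exemption covers the blue-light condition as a whole and hand scoring of recovery sleep has no stated masking, leaving the blue-light sleep comparison open to an avoidable scoring bias

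*Protocol*

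**What the plan says.** Protocol, Study design, gives the blinding scheme in one line: "Double-blind (except for blue-light), Randomized, Crossover". The Treatment section describes one means of blinding, the match between the two drinks: "Placebo and coffee will not distinguishable by taste or appearance" (sic).

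Study design also places the sleep recording after the drive, in the laboratory: "After driving, sleep recuperation will be recorded in laboratory during a minimum of 6h". Clinical assessment methods, under Polysomnography, says how it is read: "Data will be manually analyzed by an experienced sleep technician in 30-second epochs", following a published staging standard. The spectral analysis depends on that staging: "Non-rapid eye movement (NREM) sleep (stages 2, 3, and 4) during sleep will be retained for spectral analysis".

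Criteria of assessment lists three secondary efficacy criteria that come from this recording: "Sleep latency during the subsequent sleep", sleep efficiency, and the time course of slow wave activity. They serve the third secondary objective: "To determine the effects of blue light on quality and quantity of sleep after night-time driving in young and middle-aged healthy volunteers". Expected results anticipates "Modifications on quality and quantity of sleep after the blue light exposure during nighttime driving in young and middle-aged healthy volunteers".

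No section says whether the technician is kept unaware of the condition, whether recordings are coded, or whether the scorer is separate from the staff who run the sessions.

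**The concern.** A lamp in a car cannot be hidden from the person driving. A stored sleep recording is different: it is read later and shows no lamp, so the scorer can be masked in every condition. The exemption does not make this distinction. It removes the blue-light condition from the blinding scheme without saying for whom, and the scoring paragraph does not restore the protection.

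The result is lopsided. Coffee and placebo nights remain under the double-blind arrangement and blue-light nights do not. A scorer who could recognise one condition out of three could, without intending to, treat borderline epochs differently on those nights. The effect would fall on blue light versus placebo and blue light versus coffee, which are the comparisons the sleep objective needs. The objective could then report a difference in sleep that lies partly in the scoring.

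**Working it through.** The Protocol states no figure on this point, so there is none to reproduce. The check sets the provisions side by side and follows a scoring shift through the design.

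**1. Which sleep measures depend on the scorer's judgement**

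| Measure (Criteria of assessment) | How it arises (Polysomnography) | Exposure |
|---|---|---|
| Sleep latency | Directly from the epoch staged as sleep onset | Direct |
| Sleep efficiency | Directly from the sleep or wake call on each epoch | Direct |
| Slow wave activity | Computed by Fourier transform on epochs staged as NREM | Indirect, through the choice of epochs only |

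**2. Which masking provision reaches the scorer**

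- Study design: double-blind, blue light excepted, no roles named.
- Treatment: drinks matched. This masks coffee against placebo only.
- Polysomnography: manual scoring, with no coding or masking.

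No provision masks the scorer to blue light.

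**3. Whether the design removes a shift**

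Let the expected scored value in a condition be its true mean plus a scoring shift *b*. The expected within-participant differences are:

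- blue light − placebo = true difference + (*b*_BL − *b*_P)
- blue light − coffee = true difference + (*b*_BL − *b*_C)
- coffee − placebo = true difference + (*b*_C − *b*_P)

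If the scorer cannot tell coffee from placebo, *b*_C = *b*_P and the third difference is clean. If the scorer can recognise blue-light recordings, *b*_BL may differ from the other two, and both blue-light differences keep the excess. Using each participant as his own control removes differences between participants, and random order protects against order effects. Neither touches a term tied to the condition itself. The repeated-measures analysis of variance in Analyses of variables would estimate that term as part of the treatment effect. If all three conditions are scored blind, the scorer has no condition to respond to, and the shifts are equal on average and cancel.

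**4. Size: an illustration only**

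The only input from the Protocol is 48 participants (Determination of sample size). The rest is assumed: an SD of 6 to 10 minutes for the within-participant blue-light minus placebo difference in latency, and a consistent one-way shift *b* of 1 or 2 minutes (two or four 30-second epochs). For a two-sided paired z test at 5%, SE = SD/√48 and the false-positive rate is P(|Z + *b*/SE| > 1.96).

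| Assumed SD | SE | *b* = 1 min | *b* = 2 min |
|---|---|---|---|
| 6 min | 6/6.928 = 0.87 | 21% | 64% |
| 10 min | 10/6.928 = 1.44 | 11% | 28% |

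The table shows how sensitive such a comparison would be if a shift existed. It does not estimate the error rate of this trial, whose planned analysis is a three-way analysis of variance and not this test.

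**The case against.** The strongest reply is that the point rests on silence. The Protocol does not say that the technician knows the condition, attends the sessions or sees session labels. The exemption can be read as a plain consequence of an undisguisable lamp, and recordings may be coded under laboratory procedures that are not shown. This stands in part. A reader might infer that sleep will be scored unmasked, or that the blue-light results will be biased. The documents support neither. They support only that the written plan does not prevent it. An unseen statistical analysis plan is not a full answer, because masking of the scorer is a matter of conduct and cannot be restored once scoring has been done unmasked.

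A reader might also take the Expected results section as evidence that a scorer would push the readings one way. It is not: it anticipates a change and names no direction, and the objective is worded neutrally. A scorer could hold a private view, but the Protocol does not supply one.

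The inflated error rates are likewise tempting to quote as the trial's own. They follow from an assumed SD and an assumed shift. A 2-minute shift needs four epochs in the same direction on average, from an experienced scorer using standard rules. Participants kept awake until after 5 AM may fall asleep quickly, which would leave little room for it.

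Finally, the measures are secondary, and slow wave activity is exposed only through epoch selection. Both statements are correct, and they limit the weight of the point.

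**Conclusion.** The point holds as an unprotected risk. The exemption from blinding is wider than the treatment requires, and hand scoring of recovery sleep is set out with no masking of the scorer. If there were a scoring shift, it would fall on the blue-light contrasts for sleep latency and sleep efficiency, and less strongly on slow wave activity, and the crossover and the analysis would not remove it. The documents give no basis for its size or direction, so no error rate should be attached to the trial. The conclusion assumes only that staging leaves some discretion at borderline epochs and that no unseen procedure already codes the recordings. The change is worth making because it costs little. The primary endpoint lies outside this point.

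**What to change.** In Clinical assessment methods, under Polysomnography, state that recordings are exported under a random code without date, session number or condition, that recordings from all three conditions are scored blind to treatment, and that the code is broken only after scoring is locked.

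In Study design, limit the exemption: coffee versus placebo double-blind; blue light open to the driver and in-car staff; sleep scoring blinded in all conditions.

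The cost is file coding by someone other than the scorer. No extra participant, procedure or reader is needed. If masked scoring is already the laboratory's practice, stating it in these two places settles the matter.
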